#### Negative pressure wound therapy

NPWT, applied on the day of randomisation, consists of a foam dressing cut to shape and applied to the wound. An airtight seal is established with a film dressing; this is then connected to a pump which applies gentle suction to the wound. This allows the removal of fluid from the wound, which is collected in a canister attached to the pump, which is carried by the participant at all times in the bag provided. Alternatively, a self-contained system consisting of a disposable NPWT pump attached to an absorbent adhesive dressing may be used. The dressing is usually changed at least once a week, and the NPWT will be applied for 2 weeks post randomisation.

#### Decellularised dermal allograft

DCDs are prepared from split skin grafts obtained from deceased human tissue donors, which are processed and sterilised. Processing retains the normal skin structure, but removes donor cells and cell remnants meaning the graft is not rejected and functions as a permanent tissue replacement. On receipt at participating sites, the graft will be stored between 0°C and 40°C until the expiry date stated on the graft label. Prior to application the graft is soaked in a bowl of sterile saline solution for 15 min. The graft is then cut to size using sterile scissors and applied directly to the debrided wound bed, epidermal side upwards. Following application, the ulcer is covered with a non-adherent contact layer and a secondary bolster dressing or NPWT (as per randomisation). In those DFUs allocated to DCD, the wound bed is not debrided for 4 months post-treatment, unless clinically indicated, although debridement of wound edge and surrounding tissue can continue as per TAU.

### Assessments/data collection and follow-up

#### Baseline assessment

Participant demographics including date of birth, gender, ethnicity, NHS number and site of the index ulcer will be recorded.

Clinical history will be recorded including smoking history, duration and type of diabetes, number of ulcers and index ulcer characteristics, for example, first or recurrent ulcer, aetiology, existing wound therapies and Site, Ischaemia, Neuropathy, Bacterial Infection and Depth (SINBAD) classification.^24^ Initial index ulcer area tracing (using acetate) will also be obtained. Participants will be asked to complete quality of life questionnaires: DFS-SF and EQ-5D-5L.

Randomisation and application of the treatment strategy will take place after baseline assessments and questionnaires have been completed, on the same day.

Information collected post-treatment will include details of the treatment strategy applied to the index ulcer and to any other ulcers on the foot of the index ulcer, and expected AEs and serious AEs (SAEs). Post HD debridement, index ulcer area acetate tracing and photographs will be obtained.

#### Follow-up assessments

At a routine clinic assessment at week 1 and at weeks 2, 4, 12, 20 and 52 post randomisation the following assessments will be conducted by a member of the clinical research team (clinician, clinical research nurse or registered healthcare professional): healing status of the index ulcer, episodes of infection in the foot of the index ulcer (IDSA criteria), revascularisation of the index limb, index ulcer treatments and expected AEs or SAEs. In addition, at weeks 1 and 2 post randomisation, an assessment of compliance with NPWT and DCD (where applicable), and at weeks 2–52 post randomisation an assessment of reulceration of the index ulcer will be conducted. At week 2 and week 4 post randomisation, an acetate tracing and photograph of the index ulcer post sharp non-surgical debridement (where clinically indicated) will be taken; at week 4 this is conducted by a blinded assessor (clinician, research nurse or registered healthcare professional).

Participant questionnaires (DFS-SF, EQ-5D-5L and healthcare resource utilisation (HRU)) will be completed at weeks 4, 12, 20 and 52 post randomisation; the HRU questionnaire will also be completed at week 8 post randomisation.

#### Healing and reulceration assessments

Healing is defined as complete closure of the ulcer: 100% re-epithelialisation of the wound surface with the absence of drainage, confirmed by blinded assessment of index ulcer healing status at two consecutive assessments 2 weeks apart.^25^

Healing of the index ulcer will be reported in one of the following scenarios:

By the research nurse/registered healthcare professional at a research visit.During the participant’s routine appointment at the MDT DFU service clinic, podiatry clinic, GP practice nurse and/or at home by district nurses as per TAU.Participant self-reporting to the research team or to the attending clinical team in between routine appointments who will then inform the research team.

The attending clinical team will contact the research team to report the date the index ulcer was first noted as healed, who will then arrange an initial visit within 3 days of healing of the index ulcer first being reported and a 2-week follow-up visit (±3 days) with the blinded assessor to assess index ulcer healing status and conduct photography.

Reulceration is defined as recurrence of a full thickness break in the epithelium at the same location as the index ulcer.^26^ Reulceration of the index ulcer will be established either by participant self-referral to the research team, at a routine clinic or research appointment or by continuous screening of new referrals to the MDT DFU service clinic where participants will be flagged to the research team by the attending clinical team. Reulceration of the index ulcer will be confirmed by a blinded assessor, within 7 days of reulceration being reported, with reference to the photograph of the foot taken at the randomisation visit, photography undertaken and the date of reulceration of the index ulcer recorded.

### Sample size

The planned maximum sample size is 447 participants, 245 participants in phase II and 202 participants in phase III. The apportionment of participants to phase II and phase III was estimated using a series of simulation studies.

In phase II, 49 participants per treatment strategy arm and 98 participants in the TAU arm will be recruited. The target effect size in phase II is an absolute increase of 25% in the proportion of participants achieving at least a 50% reduction in wound area by 4 weeks post randomisation, assuming 39% reach at least a 50% reduction by week 4 in the TAU arm (local audit data) and 64% achieve this outcome in the treatment strategy arms.

An additional 101 participants will be recruited into each arm evaluated in phase III, corresponding to a total (phase II and III combined) of 150 in the remaining treatment strategy group and 199 in the TAU arm (total of 349 participants for evaluation in phase III).

The minimum clinically important effect size in phase III is a hazard ratio (HR) of 1.5, assuming a median time to healing of 21 weeks for the TAU arm (local audit data) and 14 weeks for the treatment strategy arms^18 27–30^ and 18.0% and 7.6% *un*healed at 52 weeks in the TAU and treatment strategy groups, respectively (assuming exponential distribution for time to healing).

Several scenarios for the power of the trial have been considered. In all cases a 10% loss to follow-up by 4 weeks and 25% loss to follow-up by 52 weeks is assumed. In the case where there is a single effective treatment strategy arm, the design has 83.9% power to recommend a truly effective treatment strategy (ie, for it to progress from phase II and for a significant result found at phase III). A treatment strategy group that progresses to phase III and which is significantly better than TAU at the two-sided 4% significance level (to control the familywise error rate at 5%) on the time to healing endpoint will be declared clinically effective.

A formal sample size review will be conducted at 52 weeks, after 220 participants have been recruited, to re-estimate the proportion of participants lost to follow-up by 52 weeks post randomisation and the final sample size. The review will allow the overall loss to follow-up to be estimated to a minimum precision ±5.7% (corresponding to half width of the 95% CI), assuming a maximum loss to follow-up of 25%.

### Progression criteria for phase III

The minimum criterion for taking treatment strategies forward into phase III will be defined as at least a 10% increase in the probability of achieving ≥50% reduction in index ulcer area at 4 weeks post randomisation above that observed for TAU, corresponding to the minimum clinically important difference (clinical opinion). If more than one treatment strategy passes this threshold at phase II then the selection criteria will be based on a combination of efficacy, safety profile and cost of treatment strategies up to 4 weeks post randomisation. The progression criteria are provided in further detail in box 2.

Box 2Phase II to phase III progression criteriaThe progression criteria for the selection of treatment strategies into phase III is based on the following process:Calculate the point estimate for the proportion of participants with ≥50% ulcer area reduction at 4 weeks post randomisation in all four arms (phase II endpoint). Drop treatment strategy arms for which this proportion is less than 10% higher (on the absolute scale) than that of TAU. That is, if the proportion for TAU is 39% then recommend dropping treatment strategies for which the proportion is less than 49%. Rank the remaining treatment strategies in order of clinical activity.Note: An absolute improvement of 10% in the proportion of participants with ≥50% ulcer area reduction at 4 weeks post randomisation corresponds to the critical cut point for the selection of treatment strategies based on clinical activity.If more than one treatment strategy has a success rate at 4 weeks of at least 10% greater than TAU then summarise SAEs and rank order of treatment strategies in terms of their safety profile. Only AEs and SAEs that are classified as expected and related to DFUs or trial treatment strategies, or ‘related and unexpected SAEs’ (RUSAEs) will be considered. Decision on whether to drop treatment strategies with the ‘least favourable’ safety profile will be made by the Data Monitoring and Ethics Committee (DMEC).If more than one treatment strategy remains after stages (1) and (2) then summarise treatment-related costs up to 4 weeks and rank order of treatment strategies by ascending cost of treatment versus TAU. Decision on whether to drop the treatment strategies with the highest cost will be made by the DMEC.If no treatment strategies remain, then recommend terminating recruitment to the trial. If one remains, take this forward to phase III. If more than one treatment strategy satisfies (1) to (3), take forward the top performing arm defined by clinical activity (the extent of improvement in the proportion of participants achieving the phase II endpoint).The trial will also have a futility rule to allow for stopping of the trial on the basis of no treatment strategy demonstrating at least 10% absolute improvement in the success rate of the phase II primary outcome. This will be non-binding to allow the DMEC to make the final recommendations to the Trial Steering Committee (TSC) on whether or not to stop the trial.

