### Blinding

Due to the nature of the treatment strategies it is not possible to blind participants, the clinicians or research team to the treatment group allocation. However, primary outcome assessments will be conducted by an independent clinical assessor with no knowledge of treatment allocation. To mitigate risk of assessment bias the blinded assessor will also have no access to participant notes or trial case report forms. Blinding will be maintained when tracings and photographs at week 4, and confirmation of the index ulcer healing assessments, are returned to the CTRU (eg, through separate mail or independent clerical staff).

For the phase II primary outcome and phase III exploratory objective, a blinded assessor at each site will complete an acetate tracing and take a two-dimensional digital photograph of the index ulcer at week 4. Measurements will be obtained from the index ulcer tracing using ‘Image J’ software^23^ by a member of the CTRU team who is independent of the research teams at recruiting sites and blind to treatment allocation. A photograph of the index ulcer will be taken as a backup in the event that a tracing cannot be taken or is of insufficient quality to determine the index ulcer outline.

For the phase III primary endpoint, all participants recruited to both phase II and III will also have a photograph taken of the reported healed index ulcer by the blinded assessor within 3 days of healing being reported and 2 weeks later as a confirmation of healing, which will undergo blinded central review.

Photographs taken of healed and of unhealed index ulcers for randomly selected participants will be submitted for central blinded photography review by clinical members of the Trial Management Group who will not be aware of the participant’s identity, treatment group or time point at which the photograph was taken.

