#### Phase II secondary endpoint analysis

AEs and SAEs that are classified as expected and related to DFUs and trial treatment strategies, or RUSAEs will be summarised by treatment group.

Mean per-patient costs of treatment, healthcare use and total resource use, together with a measure of variance will be reported by treatment group.

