#### Phase III secondary endpoint analysis

Similar regression-based analyses will be used for other secondary endpoints. Cumulative incidence of healing at 12, 20 and 52 weeks post randomisation will be obtained from the primary endpoint analysis model. A Poisson-Gamma regression model will be fitted to infection status over time. A Cox proportional hazards regression model will be fitted to time to reulceration of the index ulcer on those participants where healing of the index ulcer is confirmed. A repeated measures, random coefficients, linear regression model will be fitted to the DFS-SF Score over time.

All AEs and SAEs, including amputations and admissions to hospital, will be recorded and summarised by treatment strategy received. Expected treatment-related AEs include: pain, bleeding and infection from HD; bleeding, infection and skin irritation/breakdown from NPWT; seroma and allergic reaction from DCD.

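### The article conflicts with itself on which adverse events are collected, and the Box 2 safety step omits related unexpected non-serious events and SAEs judged unrelated

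*Protocol article*

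**What the plan says.** **Events that count at selection.** Under Progression criteria for phase III, step 2 of Box 2 opens: "If more than one treatment strategy has a success rate at 4 weeks of at least 10% greater than TAU then summarise SAEs". It then limits the eligible events: "Only AEs and SAEs that are classified as expected and related to DFUs or trial treatment strategies". The one addition is RUSAEs, that is, serious events that are unexpected and judged related. The consequence follows: "Decision on whether to drop treatment strategies with the ‘least favourable’ safety profile will be made by the Data Monitoring and Ethics Committee (DMEC").

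**Phase II safety summary.** The section Phase II secondary endpoint analysis uses nearly the same set, with a different conjunction: "AEs and SAEs that are classified as expected and related to DFUs and trial treatment strategies, or RUSAEs will be summarised by treatment group".

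**Events collected.** The Baseline assessment section lists, among the post-treatment information, expected AEs and SAEs. The Follow-up assessments section lists, for each visit, "index ulcer treatments and expected AEs or SAEs".

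**Events promised for analysis.** The section Phase III secondary endpoint analysis says: "All AEs and SAEs, including amputations and admissions to hospital, will be recorded". The Phase III secondary objectives include incidence of AEs over 52 weeks, with no restriction to expected events.

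**Who knows the allocation.** The Blinding section states that "it is not possible to blind participants, the clinicians or research team to the treatment group allocation".

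**The concern.** There are two linked problems.

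The first is a contradiction about data capture. If visits ask only for expected AEs and SAEs, the trial will not hold all AEs, and an unrestricted comparison of AE incidence cannot be made from what was collected. An analysis plan can choose what to tabulate, but it cannot recover non-serious events that no visit asked for.

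The second is the filter in Box 2. The safety step can remove an arm, so the events it admits matter. It filters on expectedness and on relatedness. The first filter removes unlisted non-serious events even when everyone agrees that the treatment caused them. The second removes SAEs attributed to neither ulcer nor treatment. The clinicians and research team know the allocation, so if they make the attribution, the second filter rests on unblinded opinion. The Introduction describes the UK allograft as novel and recently developed, and it is part of two of the three strategies, so unlisted events are a reasonable thing to look for in phase II.

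At stake is whether the DMEC sees the full safety picture when it decides whether to drop an arm.

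**Working it through.** The article states no figure on this point, so there is none to reproduce. The check is a comparison of its statements, with a short calculation for scale.

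**1. Collection against promise**

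| Section | AEs covered |
|---|---|
| Baseline assessment (post-treatment) | expected AEs; SAEs |
| Follow-up assessments | expected AEs; SAEs |
| Phase III secondary objectives | AE incidence, no limit to expected |
| Phase III secondary endpoint analysis | all AEs and SAEs |

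The first two rows and the last cannot all hold for a non-serious unexpected AE.

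**2. What Box 2 step 2 counts**

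| Event | Counted? |
|---|---|
| Expected, related to DFU or to treatment, serious or not | yes |
| Unexpected, related, serious (RUSAE) | yes |
| Unexpected, related, non-serious | no |
| SAE judged unrelated to both DFU and treatment | no |

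The last two rows are the gap.

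**3. The boundary of the set.** Box 2 joins the two kinds of relatedness with *or*; the phase II analysis section joins them with *and*. Read literally, *and* requires relatedness to both, so an expected SAE attributed to the ulcer alone would be in under Box 2 and out of the phase II summary. A looser reading makes the two sets equal, but the text does not settle it. Box 2 also opens by asking for a summary of SAEs and then admits AEs.

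**4. When the step applies.** It runs only if two or more strategies reach the 10% absolute improvement over TAU. If exactly one does, Box 2 applies no safety ranking. If several remain after the safety and cost steps, the arm taken forward is the one with the greatest clinical activity.

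**5. Scale (assumed rates; the article gives none).** The Sample size section gives n = 49 per strategy arm. For a true rate p of an unlisted, non-serious, treatment-caused event, the expected number affected is 49p and the chance of at least one is 1 − (1 − p)^49.

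| p | 49p | Chance of at least one | Contribution to Box 2 ranking |
|---|---|---|---|
| 2% | 1.0 | 63% | 0 |
| 5% | 2.5 | 92% | 0 |
| 10% | 4.9 | 99.4% | 0 |
| 20% | 9.8 | >99.9% | 0 |

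Likewise, an invented excess of 4/49 against 1/49 in SAEs judged unrelated would add nothing to either arm's count.

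**The case against.** The case for leaving the plan alone has real content, and it limits how far the point can be taken.

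- **Disease-attributed SAEs.** A reader might infer that serious events blamed on the underlying disease are excluded. Box 2 does not say that: its wording admits expected events related to the DFU, so moving the cause of an expected event from treatment to ulcer does not remove it. Only events judged unrelated to both drop out. This also weakens the worry about unblinded attribution, without removing it.
- **Only foreseen harms.** A reader might infer that nothing unforeseen can appear. RUSAEs are unexpected by definition and are counted. For related events the gap is confined to non-serious unexpected ones.
- **Safest arm wins.** A reader might infer that an arm could go forward because it ranks safest. It could not: the DMEC decides whether to drop an arm, and clinical activity decides among those left. The most that can happen is that a drop is decided, or not decided, on incomplete information.
- **Harm invisible throughout the trial.** Infection in the foot, revascularisation, index ulcer treatments and reulceration are recorded separately at visits, and amputation and hospital admission are named for analysis. For the trial as a whole the supportable finding is a conflict between statements.
- **The expected list.** The treatment-related list is introduced as what such events include, so it need not be exhaustive, and both allograft arms also carry the events listed for hydrosurgical debridement.
- **Condensed article.** Targeted collection of expected AEs plus SAEs can be deliberate, and the full protocol may define the list and name who classifies events. That is a fair reason not to criticise those absences. It does not reconcile statements that disagree, or change a rule that says only certain events count.
- **Noise.** Showing all events brings in background comorbidity, and counts at 49 per arm are weak evidence: 4/49 against 1/49 gives a two-sided Fisher p of 0.36. This argues against ranking mechanically on all events. It does not argue against showing them to the DMEC.

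**Conclusion.** The point holds in a limited form. The article's statements on which AEs are collected conflict and must be reconciled. The Box 2 safety step, as worded, leaves out related but unexpected non-serious AEs and SAEs judged unrelated to both DFU and treatment, and the wording of the restricted set differs between Box 2 and the phase II analysis section.

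The size cannot be stated from the documents. Under assumed rates of 2% to 20%, between about 1 and 10 affected participants per strategy arm would add nothing to the ranking. The consequence is confined to the case where more than one strategy passes the efficacy threshold, and to a discretionary decision of the DMEC. The concern about attribution assumes that the unblinded site teams classify relatedness; the article does not say who does.

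**What to change.** 1. Reconcile the Baseline assessment, Follow-up assessments, Phase III secondary objectives and Phase III secondary endpoint analysis sections on which AEs are collected, and apply the same collection in every arm including TAU. If targeted collection is intended, say so in the objective and the analysis section; if all AEs are intended, say so in the visit schedules.
2. Align Box 2 and the Phase II secondary endpoint analysis section on *or* versus *and*, and state in Box 2 that the summary covers AEs as well as SAEs.
3. Amend Box 2 step 2 so that the DMEC also receives all SAEs and all recorded AEs by randomised arm, irrespective of expectedness and attribution and including related non-serious unexpected AEs, alongside the expected/related subset. The subset can remain the basis of the ranking; whether to replace it, or to add free-text recording of every AE, is a trade-off for the trial team.

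The cost is wording changes and one more DMEC table, which will contain some background comorbidity events. If the team chooses to collect all AEs, there is also some extra recording at visits.

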### Statistical analysis

A statistical analysis plan for phase II and phase III final analyses will be finalised and signed off before any data analyses are conducted.

The complete case population will be used for the analysis of the phase II endpoint under the assumption that data are missing at random (MAR).^31^ A sensitivity analysis will be considered if there is differential missing endpoint data observed across treatment arms.

Phase III analyses will use intention to treat whereby participants will be analysed according to randomised treatment group. A per-protocol population will also be defined.

For phase III endpoint analyses, data from all participants recruited in phase II and phase III will be included.

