#### Phase II primary objective

To determine the efficacy of the treatment strategies:

TAU + HD alone.TAU +HD + DCD.TAU +HD + NPWT+ DCD

compared with TAU alone using the short-term intermediate outcome of achieving at least 50% reduction in index ulcer area at 4 weeks post randomisation (phase II primary endpoint).

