#### Exploratory analyses

##### Sensitivity analyses

For all analyses using the Cox proportional hazards model, the assumption of independence of the distribution of time to healing/recurrence and time to other events, that is, amputation and death will be assessed and alternative models considered if there are sufficient competing risks.

A multivariable Cox proportional hazards regression model will be fitted to explore risk factors predictive of time to healing.

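### The phase II endpoint is analysed on complete cases under MAR with no classification of death or loss of the index ulcer before week 4, so known non-responders drop out of the Box 2 comparison by default

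*Protocol article*

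**What the plan says.** The phase II endpoint is binary: "achieving at least 50% reduction in index ulcer area at 4 weeks post randomisation (phase II primary endpoint"). Under Blinding, it is measured as follows: "a blinded assessor at each site will complete an acetate tracing and take a two-dimensional digital photograph of the index ulcer at week 4". The area is read centrally from the tracing, and the photograph is a backup if the tracing is absent or unusable.

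On missing data, Statistical analysis says: "The complete case population will be used for the analysis of the phase II endpoint under the assumption that data are missing at random". It continues: "A sensitivity analysis will be considered if there is differential missing endpoint data observed across treatment arms". Intention to treat is stated for the phase III analyses only.

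Box 2 (Progression criteria for phase III) works on point estimates of the response proportions: "Drop treatment strategy arms for which this proportion is less than 10% higher (on the absolute scale) than that of TAU". Its safety ranking is reached only if more than one strategy passes that cut.

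Death and amputation appear as analysis issues in one place, Sensitivity analyses, and only for the Cox models. There the independence of healing or recurrence from "time to other events, that is, amputation and death will be assessed and alternative models considered if there are sufficient competing risks". Phase II has no counterpart.

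**The concern.** A participant who has died, or whose index ulcer has been removed by amputation, cannot supply a tracing or a photograph at week 4. Under a complete-case rule with no clause for such participants, the natural result is that they leave the denominator. Their outcome is not unknown, because they did not reach the endpoint. MAR is the wrong description for them.

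Exclusion raises the observed response proportion in any arm with more early failures, at the step where arms are dropped or selected. Later steps need not correct this:

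- If exactly one strategy passes the cut, it goes forward without the safety ranking.
- When the ranking is used, it is restricted to events classed as expected and related, or related and unexpected.
- The sensitivity analysis depends on a difference in missingness between arms. Arms can lose the same fraction for different reasons. Participants and clinicians are unblinded, so reasons for loss may differ by arm.

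Only one strategy can enter phase III, so an arm that passes wrongly can take that place from another.

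**Working it through.** **Inputs from the documents.** Sample size: "49 participants per treatment strategy arm and 98 participants in the TAU arm will be recruited". Response: "assuming 39% reach at least a 50% reduction by week 4 in the TAU arm (local audit data) and 64% achieve this outcome" in the strategy arms. Loss by week 4 is 10%, and the Box 2 cut is 10 points. Evaluable numbers: 49 × 0.9 ≈ 44 per strategy arm and 98 × 0.9 ≈ 88 on TAU.

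**Input not in the documents.** The rate of death or index-ulcer loss by week 4. Every rate q below is an assumption, expressed as a fraction of the participants who would then be analysed.

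**1. The plan's own figure.** The article gives 83.9% power when one strategy is effective.
- Phase II: the exact binomial probability that the observed difference is at least 10 points, with n = 44 v 88 and 64% v 39%, is 95.6%.
- Phase III: Schoenfeld's formula with HR 1.5, two-sided alpha 0.04, 150 of 349 on the strategy, and about 275 events (exponential healing with medians 14 and 21 weeks, 25% loss as exponential censoring) gives 89.8%.
- Product: 0.956 × 0.898 ≈ 85.9%, within 2 points of the stated figure. If lost participants contribute no events (about 226 events), phase III power is 83.3% and the product 79.6%.
- The agreement is approximate, because the article used simulation and does not give the loss pattern. No death or amputation rate enters this calculation.

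**2. Effect of the classification on the difference.** Let p_T and p_C be the complete-case proportions. Counting these events as non-response gives

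p_T(1 − q_T) − p_C(1 − q_C).

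For an arm at the cut (49% v 39%, 10.0 points on complete cases):

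| q_T | q_C | Difference (points) |
|---|---|---|
| 1% | 1% | 9.9 |
| 2% | 2% | 9.8 |
| 5% | 5% | 9.5 |
| 2% | 0 | 9.0 |
| 4% | 0 | 8.0 |
| 6% | 0 | 7.1 |
| 10% | 0 | 5.1 |

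For example, 0.49 × 0.96 − 0.39 = 0.0804.

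**3. Effect on the chance of passing.** At 49% v 39%, the chance of passing is 51.5% on complete cases. With events in the strategy arm only, at 2%, 4%, 6% and 10%, it becomes 47.1%, 42.3%, 37.7% and 28.9%. At the design effect (64% v 39%), it goes from 95.6% to 94.4% with 5% in both arms, and to 92.1% with 4% in the strategy arm only.

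**4. A worked count with equal missingness.** Suppose 44 of 49 strategy participants and 88 of 98 TAU participants have tracings. Missingness is 5/49 = 10.2% and 10/98 = 10.2%, so the plan's trigger is not met. Let responders be 22 and 34.
- Complete cases: 22/44 − 34/88 = 50.0% − 38.6% = +11.4 points. The arm passes.
- One of the five missing strategy participants is a death or amputation: 22/45 − 34/88 = 48.9% − 38.6% = +10.3. It still passes.
- Two of the five: 22/46 − 34/88 = 47.8% − 38.6% = +9.2. It fails.
- All missing counted as non-response in both arms: 22/49 − 34/98 = 44.9% − 34.7% = +10.2. It passes.

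The last line shows that an all-missing-as-non-response analysis alone would not reveal the problem here. The classification rule does.

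**The case against.** The strongest reply is that no passage says these participants are excluded. If the derivation of response codes them as non-responders, they are complete cases under the same sentence. A full protocol and a signed-off analysis plan are mentioned and could say so. This stands against the stronger reading that the plan states a rule removing deaths and amputations. A reader might infer that, but the text is silent. What the article does fix is complete case under MAR, on an endpoint that needs a week-4 measurement, with no non-response clause. Exclusion is the default effect of that.

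Second, the events may be rare. Eligibility excludes a clinically infected ulcer on the index foot, bone or joint involvement of the ulcer base, and a compressible ankle brachial index below 0.7. No event rate is given, and balanced events hardly matter. This stands, and it limits the size of the point.

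Third, a reader might be drawn to a starker example. If 15% are lost in the strategy arm and 8% on TAU, and all of them failed, an apparent 13 points (52% v 39%) becomes 0.52 × 0.85 − 0.39 × 0.92 = 8.3. The documents do not support using it here. It concerns total loss, and such a difference is the case in which the plan says a sensitivity analysis will be considered. With 10% lost in both arms and all failures, the result is 0.9 × 13 = 11.7 points and the arm still passes. The equal-missingness count in the working does not depend on this example.

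Fourth, phase II only screens. Effectiveness is declared on phase III time to healing at the two-sided 4% level, so an arm that passes wrongly does not become a positive result. This also stands. The cost is a misused or displaced phase III place.

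**Conclusion.** The point holds as a gap in a stated rule that has a predictable default effect. Complete case under MAR is fixed for the endpoint that drives Box 2, known early failures are not classified, and the conditional sensitivity analysis cannot be relied on, because equal missingness does not establish MAR.

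The size depends on event rates that the documents do not give. For an arm at the cut, the shift is 0.5 points or less if events are balanced at 1% to 5%. It is 2 points if 4% occur in the strategy arm only. Near the cut, two unbalanced failures can change the decision, as 22/44 against 22/46 shows. An arm well above the cut is little affected.

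A reader might infer that the 83.9% power is undermined. It is not: the figure is approximately reproduced without any death or amputation rate. This should be corrected, but it does not threaten the phase III inference.

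**What to change.** State in the primary phase II analysis, and in the first step of Box 2, that death, or amputation or surgery that removes the index ulcer, before the week-4 assessment counts as non-response. Treat only the remaining missing tracings as MAR.

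Replace the conditional sensitivity analysis with one that is always given to the DMEC for the Box 2 differences, for example all missing counted as non-response, whether or not missingness differs by arm. Keep it supportive. It shrinks every difference (10 points becomes 9 at 10% loss in both arms), and in the count above it would still have passed the arm. It should therefore not replace the primary rule.

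The cost is about two sentences. The small downside is that a few unrelated early deaths count as non-response, in all arms alike. If the full protocol or the analysis plan already classifies these events this way, the article and Box 2 need only say so.
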